**Fig. 1 Fig1:**
[figure not shown]
Local of TUS application (patellar tendon)

A program of therapeutic exercises was developed based on clinical features [40–42] and specific strategies for patellar tendinopathy management [4, 43] and also in similar exercises [44, 45] and protocols applied in other overload conditions [46]. This program will be delivered in four phases, each one containing 2 weeks duration [20, 35, 47] (Tables 1 and 2) and the standardized sessions will be performed in individually and will be supervised by the same physical therapist that is also responsible for all TUS applications. The participants will be instructed not to use other interventions, but will be encouraged to stay active in their physical activities or sports during this program, however respecting their level of function and pain. This information will be given to the participants at the initial examination.

### Outcome measure

Pain intensity will be measured using the Visual Analogue Scale (VAS) [48, 49]. This outcome will be always based on routinely presented pain (VAS-usual) and pain during the eccentric decline squat (VAS-irritative at pre-TUS and post-TUS) [27, 50]. Pain, dysfunction and the level of physical activity will be measured with the VISA-P questionnaire [34] and the International Physical Activity Questionnaire-Short Form (IPAQ-short form) [51], respectively.

The trunk and lower limbs kinematics will be assessed with two-dimensional (2D) kinematic analysis, once patellar tendinopathy may cause kinematic changes at hip [33, 52], knee [53, 54] and foot [53, 54] levels during landings the 2D-kinematics analysis will be applied in attempt to detect lower limb and trunk kinematic patterns on different types and intensities of landing tasks in both groups.

The acquisition of these images will be carried out with two cameras Optitrack (NaturalPoint Inc., Corvallis, OR, USA) with 0.3 MP resolution and capture rate of 100 FPS, two cameras (color video capture) Logitech - Model: C920 (Logitech, Newark, CA, USA) with 3 MP resolution and capture rate of 30 FPS and with the software myoVIDEO - MR3 3.6.43 (Noraxon USA Inc., Scottsdale, AZ, USA). Reflective markers will be applied on the acromion bilaterally, manubrium, xiphoid process, antero-superior iliac spines, patellar bases, ankle joint lines, major trochanters, lateral femoral condyles of the knees, lateral malleoli, intermediate third of the fibula diaphysis, and on the tuberosity of the fifth metatarsals [55, 56].

The following movements will be verified and quantified in the frontal plane: trunk inclination, pelvic tilt, hip adduction, and knee valgus; and in the sagittal plane: trunk flexion, hip flexion, knee flexion, and ankle dorsiflexion. The time to acquire the peak knee flexion will also be quantified. The motion cameras for the frontal and sagittal planes will be placed 3.5 m and 3.0 m from the participant, respectively, for data collection on Single Leg Squat (SLS) [55, 57] and Drop Vertical Jump Test - Double and Single Leg (DVJ-DL and DVJ-SL) [55, 58]. For the Single Hop Test for Distance (SHTD) [59], the cameras will be placed 3.7 m and 3.0 m from the participant for frontal and sagittal plane data collection, respectively. The motion analyses will be performed at peak knee flexion, as this moment will be the reference for all measurements.

The strength (maximum voluntary isometric contraction, MVIC) of the gluteus maximus [42, 60] (hip extension), gluteus medius [61] (hip abduction), quadriceps femoris [59] (knee extension), and triceps surae [42] (ankle plantar flexion) will be assessed with a handheld dynamometer (Manual Muscle Tester, model 01163, Lafayette Instrument Company, Lafayette, IN, USA) [62]. A nylon belt will be positioned perpendicular to the dynamometer during the tests in order to stabilize the dynamometer and to resist the force generated by the participant. Two 5-s MVIC will be performed with a 30-s interval between contractions [59]. The average strength of each muscle - obtained in kilogram/force (KgF) - will be normalized by the body weight of each participant, using the following formula: (muscle strength kg/ body weight kg) X 100 [59].

Pain pressure threshold (PPT)-algometry (PPT – algometer model: DD-2000, Instrutherm, São Paulo, SP, Brazil) of the patellar tendons will be performed at T0, T1 and T2 evaluations time-points and at every session – before and after the TUS application (± 8′ interval between PPT evaluation). For this measurement, the participant will be positioned in supine, with the knee flexed (± 20°) and stabilized with a positioning cushion and as soon as the individual experienced a painful/discomfort sensation he/she will say “stop”; the PPT algometer will be immediately released and the force (in Newtons) will be read from the display. The data will be collected twice (the average will be used) directly on the patellar tendon (just below the apex of the patella) [63].

There is more specific information about 2D kinematic analysis, muscle strength dynamometer and PPT algometry at Additional file 1.

Thermography of the patellar tendons will be assessed with the thermal camera FLIR C2 (FLIR Systems Inc., Danderyd, Sweden), which has a resolution of 320X240 pixels and in accordance with international recommendations [64]. Two images will be captured, and the average of the two images will be used. Before collecting data on thermography, participants will remain for 10 min in a room at ambient temperature. The camera will be positioned perpendicular to the patellar tendon at a distance of approximately 30 cm [65–68].

Possible tissue changes of the patellar tendons or adverse events will be assessed by magnetic resonance imaging (MRI) at two separate time points: before (T0; initial MRI) and after the treatment program (T2-final MRI). The images will be acquired in a magnetic field of 1.5 T (high field). The MRI protocol will consist of proton-density (PD) T2-weighted fast spin-echo (FSE) sequences acquired in the coronal, axial, and sagittal planes, with pulse sequence and cuts of 3 mm thickness, 0.3 mm inter-cut space, repetition time (TR) of 3760 ms, echo time (TE) of 16.25 ms and 97.54 ms, respectively, without averages, field of view (FOV) of 150 X 150 X 106 mm, 32 cuts with acquisition matrix of 256 X 256, resulting in 0.586 mm of plane resolution [69, 70]. The following characteristics will be assessed: intra-tendinous signal, involvement to the retropatellar region (Hoffa’s fatpad), tendon volume, the area of the maximum transverse section of the tendon, maximum antero-posterior tendon diameter, and signal intensity [70, 71]. A physician will perform the MRI assessments with clinical experience in imaging analysis, with no knowledge of group allocation or MRI order (initial or final).

### Data collection

After recruitment and before the beginning of treatments, demographic/personal data, clinical history (duration of symptom), and patellar tendon morphological characteristics (initial magnetic resonance imaging - MRI) will be collected.

The outcomes of this study (Table 4) will be collected in five time-points: before starting the program (baseline – T0), in the middle (after 4 weeks/8 sessions – T1), in the end (after 8 weeks/16 sessions – T2), three and 6 months after the end of the program (follow-ups T3 and T4, respectively). The T3 and T4 data collection will be performed by mobile text messages, telephone contact or mail (depending on participant preference). However, the primary time points will be baseline (T0) and the end of the program (T2).

**Table 4 Tab4:** Outcome measured and time-points

Outcomes	Data collection time-points					
	T0^a^	All sessions	T1	T2^a^	T3	T4
Primary						
1. VAS	X	X	X	X		
2. VISA-P	X		X	X	X	X
Secondary						
3. IPAQ-short form	X		X	X	X	X
4. PPT algometry	X	X	X	X		
5. Thermography	X	X	X	X		
6. Muscle strength	X		X	X		
7. 2D kinematics	X		X	X		
8. MRI	X			X		

^a^ Primary time-points

*VAS* Visual analogue scale; *VISA-P* Victorian Institute of Sports Assessment-Patella; *IPAQ-short form* International Physical Activity Questionnaire-Short Form; *PPT* Pain Pressure Threshold; *2D kinematics* two-dimensional kinematic analysis; *MRI* Magnetic resonance images

Beyond that, in all sessions will be collected VAS[48, 49]-usual, VAS-irritative: pre- and post-TUS [4]; and thermography: pre-TUS, post-TUS, pre-quadriceps exercises, and at the end of the session. The MRI will only be acquired at the beginning and at the end of treatment program.

An assessor who will be unaware of each participant’s group allocation will collect all these outcomes. Figure 2 shows the flowchart with a summary of experimental procedures and the participation of individuals, according to the Consolidated Standards of Reporting Trials (CONSORT) [72].

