## Abstract

**Background:**

Patellar tendinopathy is an extremely debilitating condition and its treatment usually requires a combination of clinical approaches. Therapeutic ultrasound (TUS) is one of the most available electrophysical agent in rehabilitation settings; however, there is also a lack of high-quality studies that test different dosimetric aspects of TUS. Thus, the purpose of this study is to evaluate the short-, medium-, and long-term effects of the combination of high-energy TUS with a rehabilitation program for patellar tendinopathy.

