**Methods:**

This will be a randomized, placebo-controlled trial with blinding of patients, assessors, and therapist. The setting is an outpatient physical therapy clinic. We will recruit 66 participants (male and female) aged between 18 and 40 years and presenting with patellar tendinopathy. A treatment combining high-energy dose TUS and a rehabilitation program for patellar tendinopathy will be delivered twice a week for 8 weeks. The control group will receive the same treatment, but with a placebo TUS. The effectiveness of the intervention will be measured at the beginning (baseline), midpoint (4 weeks), and end of treatment (8 weeks), as well as at 3- and 6-months post-treatment. Primary outcomes will be pain intensity (visual analogue scale, VAS), and VISA-P questionnaire and primary time points will be baseline (T0) and the end of the program (T2). Also, IPAQ-short form questionnaire, muscle strength (manual dynamometry), 2D kinematics, pain pressure threshold (PPT) algometry, thermography, and magnetic resonance imaging (MRI) will be collected.

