## Methods

### Aim

The aim is to compare the effects in short-, medium-, and long-term of high-energy TUS or its placebo with a rehabilitation program for patellar tendinopathy.

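### Long-term effects are promised, but VAS pain intensity is not scheduled after T2, so durability rests on the combined VISA-P score alone

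*Protocol article*

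**What the plan says.** The Background paragraph of the abstract gives the purpose as to "evaluate the short-, medium-, and long-term effects of the combination of high-energy TUS with a rehabilitation program", and the Aim section repeats it: "The aim is to compare the effects in short-, medium-, and long-term of high-energy TUS or its placebo". The abstract's Methods paragraph says that effectiveness is measured at baseline, 4 weeks and 8 weeks, "as well as at 3- and 6-months post-treatment". It then states: "Primary outcomes will be pain intensity (visual analogue scale, VAS), and VISA-P questionnaire". The primary time points are T0 and T2.

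The Data collection section says: "The outcomes of this study (Table 4) will be collected in five time-points". It lists T0, T1 (after 8 sessions), T2 (after 16 sessions), T3 (3 months after the end of the program) and T4 (6 months after). Of the last two it says: "The T3 and T4 data collection will be performed by mobile text messages, telephone contact or mail".

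Table 4 marks VAS at T0, all sessions, T1 and T2, and leaves T3 and T4 empty. VISA-P and IPAQ are marked at all five time points.

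The Outcome measure section gives VAS two components: usual pain, and pain during the eccentric decline squat, the latter taken before and after TUS. On the questionnaires it says "Pain, dysfunction and the level of physical activity will be measured with the VISA-P questionnaire" and IPAQ respectively, so VISA-P stands for pain and dysfunction and IPAQ for physical activity.

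**The concern.** Pain intensity is one of two primary outcomes, and the aim reaches beyond the end of treatment. The abstract places the 3- and 6-month measurements directly before the list of primary outcomes, so a reader would expect pain intensity at follow-up. Table 4 provides none.

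If VAS favours active TUS at T2, the obvious next question is whether that advantage persists once the sessions stop. The planned data cannot answer it on the VAS scale. No analysis plan can recover values that were never collected. The trial is described as ongoing, so each follow-up contact that passes without VAS is lost.

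**Working it through.** This is mainly a comparison of the schedule with the aim. The sample size was also checked, to see whether it depends on the gap.

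**1. Schedule against the stated time points (Table 4).**

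| Outcome | T0 | Sessions | T1 | T2 | T3 | T4 |
|---|---|---|---|---|---|---|
| VAS (primary) | X | X | X | X | – | – |
| VISA-P (primary) | X | – | X | X | X | X |
| IPAQ | X | – | X | X | X | X |
| PPT algometry | X | X | X | X | – | – |
| Thermography | X | X | X | X | – | – |
| Muscle strength | X | – | X | X | – | – |
| 2D kinematics | X | – | X | X | – | – |
| MRI | X | – | – | X | – | – |

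Outcomes collected at all five time points: 2 of 8. Primary outcomes collected at T3 and T4: 1 of 2. VAS is collected at 3 of 5 time points.

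**2. Are the blank cells real?** The VAS and PPT rows carry the same marks. The Outcome measure section confirms the PPT schedule in prose (T0, T1, T2 and every session). The VISA-P and IPAQ rows do show marks under T3 and T4. The columns are therefore aligned, and the blanks are the plan and not a fault of text extraction.

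**3. Does remote follow-up explain the gap?** T3 and T4 take place by text message, telephone or mail. That accounts for the absence of MRI, kinematics, dynamometry, algometry and thermography. It also accounts for VAS-irritative, which needs the decline squat and is tied to the TUS application. It does not account for VAS-usual, a self-report of routine pain that could go into a contact already collecting two questionnaires.

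**4. What can be estimated.**
- VAS, group difference at T2: yes. VAS is marked at T2, after session 16.
- VAS, group difference at T3 or T4: no data.
- VISA-P, group difference at T3 and T4: yes, as a combined score. The article defines no separate pain score from it.

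**5. Does the sample size depend on this?** Inputs from the data analysis section: VISA-P difference 12.2, SD 16.2, α 0.05, and 80% (labelled as β-error, read here as power). Assuming a two-sided test:

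n per group = 2 × (1.960 + 0.842)² × (16.2 / 12.2)² = 2 × 7.85 × 1.763 ≈ 27.7, rounded up to 28.

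With 15% losses: 28 / 0.85 = 32.9, rounded up to 33 per group, or 66 in total. Both stated figures reproduce. The article says that VISA-P required the larger number, so neither the absence nor the addition of VAS at T3 and T4 changes the sample size.

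**The case against.** The strongest reply is that durability is already measured. VISA-P is itself primary, covers pain by the article's own description, drove the sample size and is collected at T3 and T4. A reader might infer from the blank cells that the trial says nothing about lasting pain relief. The documents do not support that, because VISA-P gives pain-related evidence at both follow-ups. What remains is narrower: VISA-P mixes pain with dysfunction, and the trial chose VAS as a separate primary measure of pain intensity.

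A reader might also infer that the primary analysis is damaged. It is not. The primary time points are declared as T0 and T2, and VAS is present at both. Nor does VAS recording stop with the last TUS session, since T2 follows session 16. The gap begins after T2 and runs through the 6 months to T4.

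The sentence on five time points points to Table 4, and the same section says that MRI is taken only at the beginning and end. It is better read as a loosely worded list of visits than as a promise of every outcome at every visit. The article also never assigns short, medium and long term to particular visits, so only the post-treatment period can be said to lack VAS.

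Finally, the remedy is not free of difficulty. VAS is defined with two components, and only one can be collected remotely. A visual scale cannot be marked over the telephone, and the contact mode varies with participant preference. These points stand, and they shape the fix. They do not explain why VAS-usual was left out.

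**Conclusion.** The point holds in a limited form. The aim and abstract promise long-term effects with follow-up at 3 and 6 months, yet one of the two primary outcomes has no scheduled value at either visit. The trial cannot estimate whether a between-group difference in VAS pain intensity lasts beyond T2. Only the combined VISA-P score speaks to the durability of symptoms.

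The extent is VAS absent at 2 of 5 time points for all 66 planned participants. The primary T0 to T2 comparison and the 28 (33 with losses) per group stand. The gap concerns the long-term part of the aim.

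The conclusion rests on Table 4 being the operative schedule, and on VAS-usual being obtainable by self-report at a remote contact.

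**What to change.** **Preferred.** Mark VAS-usual at T3 and T4 in Table 4, collected in the same contact as VISA-P and IPAQ. Leave VAS-irritative out. Fix one remote response format for all participants that works by text, telephone and mail alike. Estimate the between-group difference at T3 and T4, with its 95% confidence interval, as a secondary analysis within the planned group-by-time mixed model.

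**Cost.** A short amendment and one added item in a contact that already takes place. The small downside is the move from in-person to remote scoring after T2. It applies equally to both groups, so the between-group difference at T3 and T4 remains a like-for-like comparison, but change from T2 to T3 within a group would be partly a change of mode and should be read with that in mind. Participants already past T3 or T4 will have missing values, and their number should be reported by group.

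**If VAS-usual is not added.** State in the aim and abstract that effects after T2 are assessed by VISA-P and IPAQ only, and reword the sentence on five time points so that it matches Table 4. This costs a text edit.

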**Fig. 2 Fig2:**
[figure not shown]
CONSORT study flowchart

### Data analysis, monitoring, and auditing

The sample size was calculated using the primary outcome variables: VAS and VISA-P questionnaire. A higher number of participants per group was required when the calculation was performed using data from the VISA-P questionnaire. For the calculation, the minimum detectable difference (MDD) considered was 12.2 points [34], with an average of the standard deviations of 16.2 points [27], resulting in 28 participants per group for an α-error of 0.05 and a β-error of 80%. Thus, 33 participants per group (assuming 15% of possible sample losses) will be selected.

The head-coordinator ([name]) of the present study will be the responsible for the monitoring and auditing process of all stages related to this clinical trial, as well as be responsible for terminate it. These processes will be performed at regular times by personal visiting of data setting collection and checking the data bank archive, and if some irregularity or adverse event is detected; the trial will be interrupted.

All assessment forms will be scanned and stored in a safe place, and the data tabulation will be stored on the study’s computer and on pen drives to avoid losses. The participants will be coded by numbers to maintain the confidentiality of their personal data, which will not be disclosed. One of the researchers ([name]) will certify the data collection stage. The final results of the study will only be revealed upon completion of all follow-ups, and only the authors of the research will have access to the data prior to publication in a peer-review journal. The data will be entered twice to avoid tabulation errors, and the statistician will receive the coded data and will be blind to group allocation.

The statistical analysis will be conducted following the principles of intention-to-treat analysis [73]. The normality of the data will be tested with visual inspection of histograms and the characterization of participants will be calculated using descriptive statistics. Improvements from baseline (T0) until the rehabilitation program final time-point (T2) will be assessed with a mixed model ANOVA (split-plot ANOVA). The differences between groups (treatment effects) and their respective confidence intervals (95% CI) will be calculated for all outcomes, using mixed linear models for the interaction of groups by time. These analyses will be carried out using statistical software (Statistical Package for Social Sciences (SPSS) version 15.0).

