### Randomization and masking

All participants will be informed about the study procedures and then they will be randomly allocated to one of the intervention groups (active TUS or placebo TUS). The researcher not involved with the data collection will allocate the participant using numbers (1 or 2) placed according to the sequence presented in the plan and sealed in opaque envelopes without stratifications or covariates consideration. The randomization sequence was created at http://www.randomization.com, in a single block with two distinct labels: 1 and 2 (referring to the two groups of this study).

Participants and the therapist will be blinded throughout the treatment. To ensure blinding, two identical TUS machines will be used, however one will have its software modified by the manufacturer to simulate sound wave emission (30 s of stimulation followed by an undetectable pause in the sound wave emission) and only a researcher who is not involved in collecting data knows if the equipment is active or placebo. Furthermore, and to keep the therapist blinded, the sessions outcomes: visual analogue scale (VAS) – VAS-usual and -irritative, pain pressure threshold (PPT)-algometry, and thermography will be collected by an assessor (not the therapist) who will be unaware of each participant’s group allocation; and the treatment room will be set up by a research assistant with only one TUS equipment (in agreement with participant group allocation: active or placebo). The participants will be informed before the treatment about the characteristics of the rehabilitation program and asked to not discuss the TUS application with the therapist and assessor researchers.

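### The treatment effect is an unadjusted difference in change from baseline; adjusting for the T0 value already collected would give more precision at no cost, and the protocol should say which SD the 16.2 is

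*Protocol article*

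**What the plan says.** Under Data analysis, monitoring, and auditing, the article assesses improvement from T0 to T2 with a split-plot ANOVA. It then obtains the group differences and 95% confidence intervals for all outcomes "using mixed linear models for the interaction of groups by time". Data collection and Table 4 make T0 and T2 the primary time points, and every listed outcome has a T0 value. No baseline covariate is mentioned, and nothing says that the T0 means are constrained to be equal between groups.

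The sample size is driven by VISA-P. It uses a difference of 12.2 points, "with an average of the standard deviations of 16.2 points [27], resulting in 28 participants per group", with alpha 0.05 and a figure of 80% that only works as power. Then "33 participants per group (assuming 15% of possible sample losses) will be selected". No T0–T2 correlation is given. Under Randomization and masking, allocation is made "without stratifications or covariates consideration".

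**The concern.** When T0 is one of the modelled outcome times, the group-by-time contrast between T0 and T2 is the between-group difference in mean change. It subtracts the whole baseline value, whatever the correlation between baseline and outcome. That has two consequences.

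- **Precision.** Subtracting the full baseline adds more noise than it removes when the correlation is low. It is never more efficient than regressing on baseline.
- **Imbalance.** Allocation is unstratified with 33 per group, so chance differences in T0 VISA-P are to be expected. A change score removes too much of such a difference, because part of it would have regressed away in any case.

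The sample size compares two independent means with one SD. Whether that SD is the one that governs the planned contrast depends on what 16.2 describes, and the text does not say. At stake are wider confidence intervals than necessary and a power statement that cannot be tied to the named analysis.

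**Working it through.** **Inputs from the protocol article.** Difference 12.2; SD 16.2; alpha 0.05, taken as two-sided because one-sided gives 22 per group; power 80%; 28 evaluable and 33 recruited per group; 15% losses.

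**Assumptions not in the document.** T0–T2 correlation rho, shown as a range; equal SD at T0 and T2 unless stated otherwise.

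**Step 1: reproduce the plan's figure.** n = 2 × [16.2 × (1.960 + 0.842)/12.2]² = 27.7, so 28 per group. 28/0.85 = 32.9, so 33. Power at 28 per group is 80.5% by the normal formula and 79.0% by the t-test. The stated size follows from its own inputs.

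**Step 2: relative precision (does not depend on what 16.2 is).** With common SD σ:

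- variance of change: 2σ²(1 − rho)
- residual variance after baseline adjustment: σ²(1 − rho²)
- ratio of change to adjusted: 2/(1 + rho)

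The ratio exceeds 1 for every rho below 1. Adjustment saves 35% of the variance at rho 0.3, 25% at 0.5 and 15% at 0.7.

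**Step 3: power if 16.2 is a score SD, equal at both times.** SD of change = 16.2 × √(2(1 − rho)); adjusted SD = 16.2 × √(1 − rho²). Each goes into the same two-group power calculation. Cells show normal / t.

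| rho | SD of change | Change, 28 per group | Change, 33 per group (t) | Baseline-adjusted, 28 per group | Variance ratio |
|---|---|---|---|---|---|
| 0 | 22.91 | 51.3% / 49.9% | 56.8% | 80.5% / 79.0% | 2.00 |
| 0.3 | 19.17 | 66.3% / 64.8% | 72.1% | 84.0% / 82.7% | 1.54 |
| 0.4 | 17.75 | 73.0% / 71.4% | 78.5% | 86.7% / 85.5% | 1.43 |
| 0.5 | 16.20 | 80.5% / 79.0% | 85.4% | 90.2% / 89.2% | 1.33 |
| 0.6 | 14.49 | 88.3% / 87.2% | 92.0% | 94.1% / 93.3% | 1.25 |
| 0.7 | 12.55 | 95.3% / 94.7% | 97.3% | 97.6% / 97.2% | 1.18 |

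The change contrast reaches exactly 80% at rho 0.494 (normal) or 0.512 (t) with 28 per group, and at 0.42 (t) with all 33 retained.

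**Step 4: power if 16.2 is a change SD.** The planned contrast then has the 80.5% of Step 1 whatever rho is. The adjusted SD is 16.2 × √((1 + rho)/2), which is 14.0 at rho 0.5, so adjustment still gains.

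**Step 5: chance imbalance.** If 16.2 is the T0 SD, the standard error of the baseline difference with 33 per group is 16.2 × √(2/33) = 4.0 points, a 95% range of about ±8. Given a baseline difference D, the change estimate is shifted by −(1 − rho) × D. At rho 0.5, an 8-point imbalance moves it by 4 points, against a target of 12.2.

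**The case against.** The strongest case against runs as follows.

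- **The planned contrast is valid.** Over randomisation, a difference in change is unbiased and controls type I error. The over-correction in Step 5 is conditional on an observed imbalance and is not bias of the design. This stands in full.
- **No power failure is shown.** A reader might infer that the stated 80% fails, or that 28 per group is wrong. The document does not support that. It does not say that 16.2 is a score SD, the cited source is not available, and no correlation is given. The 28 also reproduces from its inputs. This stands.
- **The 0.5 threshold is not a property of the trial.** It assumes equal SDs. Entry requires VISA-P below 80 with no such limit at T2, so the SDs may differ. If 16.2 is the T2 SD and the T0 SD were 12 (illustrative), break-even is 12/(2 × 16.2) = 0.37. If 16.2 averages 12 and 20.4, it is (12² + 20.4² − 16.2²)/(2 × 12 × 20.4) = 0.61. This stands.
- **A short article may leave covariates to the analysis plan, and a model with T0 means constrained equal is also a group-by-time model.** This stands only in part. The article does not merely omit a covariate list. It names the estimator, and its companion split-plot ANOVA treats T0 as an outcome. On a plain reading that is an unadjusted change contrast.
- **Unstratified allocation is legitimate.** Agreed. It is relevant only because it leaves baseline imbalance to be handled in the analysis.

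**Conclusion.** The named analysis is a sound but inefficient use of the baseline data. The loss of precision holds at every correlation below 1 when the SDs are equal: the variance is 1.54 times larger at rho 0.3, 1.33 at 0.5 and 1.18 at 0.7. With unequal SDs the excess variance is (SD at T0 − rho × SD at T2)², which is never negative, so adjustment does not lose apart from the small cost of estimating one slope.

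The link between the stated power and the planned contrast is unresolved rather than broken. Under the score-SD reading, with equal SDs and 28 evaluable per group, about 80% needs rho of about 0.5 or more (0.42 with 33), while the adjusted analysis has about 80% at rho 0 and more above it. Under the change-SD reading the stated power holds throughout. The document does not settle which reading applies, so neither underpowering nor a sample-size error can be claimed. This is a free improvement, not a required correction.

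**What to change.** Define the primary treatment effect as the between-group difference in VISA-P at T2 adjusted for T0 VISA-P. ANCOVA does this, as does a mixed model on the post-baseline visits with baseline as a covariate, or a mixed model with T0 means constrained equal across groups. Do the same for VAS and the other outcomes with a T0 value. In the sample-size paragraph, state whether 16.2 is the SD of a score or of a change, and that the 80% power refers to the adjusted T2 contrast.

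The cost is a change of analysis wording, with no new data and no extra participants. The trial is described as ongoing and the statistician is to work blind to allocation, so the choice should be recorded before unblinding. Made later, it would look like selection between two estimates.
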